### Randomisation and group allocation

A researcher not otherwise involved with the trial will use computerised sequence generation with permuted block randomisation, stratified for parity (nulliparous, parous), to develop the randomisation sequence that will be applied through sequentially numbered, sealed, opaque envelopes. Those women whose CTGs meet the inclusion criteria will be randomised in a 1:1 ratio to the CTG-only group or the CTG + lactate group. Clinical care during labour and birth will continue with the woman’s obstetric and midwifery team. Neonatal care will be the provided by the neonatal team, according to national resuscitation guidelines.

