#### Women’s experiences

We developed a questionnaire of women’s experiences with labour, monitoring and research specifically for our fetal oximetry trial, drawing on key concepts from experts and peer-reviewed literature [51]. The Cronbach’s alpha (0.83 in each of the study groups) and item-total correlation (*p* < 0.001) supported the reliability and validity of the questionnaire. We will use the nine questions of the ten in the original survey [51] that are relevant to this lactate trial. These questions will seek a rating of “poor”, “fair”, “good” or “excellent” in regard to three domains:(i)labour(ii) monitoring of fetal well-being during labour and(iii) participation in the research.

Provision will also be made for free-text comments. The questionnaire will be administered by the research midwives. It will be returned via the internal hospital mail if completed prior to discharge. If the woman has been discharged without being given a questionnaire, we will contact her by phone or mail to send a questionnaire and postage paid envelope for its return. We will follow women up with one phone call or letter if the questionnaire is not returned.

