### Sample size calculations

Data from the systematic review of CTG + FBS trials and observational data from Australian hospitals support a conservative estimate of up to a 40 % relative risk reduction in caesarean sections when FBS is added to CTG monitoring [12, 27, 28]. Based on a conservative 35 % relative reduction in Caesarean Section, from 38 % of women who exhibit a non-reassuring CTG during labour to 25 %, a sample size rounded up to 300 in each group is required (total 600, alpha 0.049 (to allow for one interim analysis), power 90 %). The trial would also have 92 % power to detect a 25 % reduction in combined operative births (caesarean + vacuum + forceps) from 55 % to 41 % [12].

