### Analysis

The consultant statistician for the interim analysis will present data to the data monitoring committee in unlabelled study groups. The data management team will remain blinded to group allocation until the final analysis. Analysis will be by intention to treat and all randomised subjects will be included. Demographic information will be summarised for the groups using descriptive statistics, to ensure the groups are comparable. Proportions will be compared by Chi-squared analysis, risk ratios and their 95 % confidence intervals. Continuous variables will be compared by t-tests or their non-parametric equivalent. Logistic regression will compare the between-group difference in caesarean section. Time to event data will be analysed by Kaplan-Meier statistics. Women’s scores from the maternal perceptions questionnaire will be compared for the two groups using Wilcoxon signed rank test.

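### The plan names a paired test, the Wilcoxon signed rank test, for questionnaire scores from two independent groups; it should name the rank-sum test

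*Protocol article*

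**What the plan says.** The Analysis section gives the questionnaire its own sentence: women's "scores from the maternal perceptions questionnaire will be compared for the two groups using Wilcoxon signed rank test". Under Randomisation and group allocation, eligible women "will be randomised in a 1:1 ratio to the CTG-only group or the CTG + lactate group", using "permuted block randomisation, stratified for parity (nulliparous, parous". No matching is described there or elsewhere.

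Under Women's experiences, the questionnaire has nine items, each rated on four ordered levels from poor to excellent. They cover labour, fetal monitoring and taking part in the research. It is handed out or sent after the birth. Non-return is foreseen: "We will follow women up with one phone call or letter if the questionnaire is not returned". No baseline or repeat administration is described. Maternal satisfaction with fetal monitoring is listed under Secondary study endpoints.

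The only other non-parametric wording in the Analysis section is a general rule: "Continuous variables will be compared by t-tests or their non-parametric equivalent".

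**The concern.** The signed rank test takes one difference per pair, ranks the absolute differences and asks whether they are centred on zero. It suits a before-and-after comparison or matched subjects. Two unmatched randomised groups, each woman measured once, provide no such differences. The two-sample counterpart is the rank-sum test, which has a similar name but a different input.

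The signed rank test is the only method the article names for this questionnaire. An analyst would have to invent pairs in order to follow it, or depart from a published plan in an unblinded trial. The comparison is of real interest, because the article's Background acknowledges that scalp sampling can be uncomfortable and intrusive for the mother.

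**Working it through.** The error follows from the design, so the main check is to set the sections side by side. The article states no figure on this point to reproduce.

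**Is there anything to pair?**

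1. *Between women.* Allocation is individual and 1:1. Permuted blocks balance the numbers in each arm, and stratification balances parity; neither links a woman in one arm to a particular woman in the other.
2. *Within a woman.* A paired test would need two scores per woman. The questionnaire looks back on labour and is described as completed once. The sentence also states that the comparison is between the two groups, which rules out a within-woman reading.
3. *Rescue by another sentence.* The general non-parametric rule covers continuous variables. The questionnaire items are four-level ordinal ratings with a specific sentence of their own, which the general rule does not override.

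The named test therefore has no valid input in this design.

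**What would literal use do?** (illustration only)

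Taken from the article: four rating levels, and the planned group size ("a sample size rounded up to 300 in each group is required"). Assumed, because the article does not give them: the rating distribution, and the numbers returned. The ratings used were 5/15/40/40% in one arm, with either the same in the other (null) or 4/11/37/48% (a modest shift). All 300 per arm were taken as returned, with 2,000 simulated trials per scenario and a two-sided 5% level.

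| Method | Rejection rate, null | Rejection rate, shift |
|---|---|---|
| Rank-sum | 5.6% | 58% |
| Signed rank, random pairing | 5.6% | 54% |
| Signed rank, both arms sorted by score before pairing | 73% | 96% |

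The simulation standard error at a true 5% is √(0.05 × 0.95 / 2000) = 0.5 percentage points, so 5.6% is compatible with the nominal level. The sorted row's 96% is not usable power, because the same procedure rejects 73% of the time when there is no difference.

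*Same data, different pairing.* One data set drawn under the shift gave a rank-sum p of 0.096. Re-pairing the same women at random 2,000 times gave signed-rank p-values from 0.031 to 0.131, with a central 95% range of 0.046 to 0.106. A second data set, with 220 assumed returns per arm, gave a rank-sum p of 0.139 and a central 95% signed-rank range of 0.085 to 0.186. Pairing alone moved p across 0.05 in the first data set; in the second, the reported range stays above 0.05.

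*Ties.* Under the null ratings, the chance that two randomly paired women give the same rating is 0.05² + 0.15² + 0.40² + 0.40² = 0.345. The form of the test used here discards zero differences, so about 0.345 × 300 ≈ 104 of 300 pairs would contribute nothing.

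*Unequal returns.* With 240 and 225 returns the test could not be computed. Forcing 225 pairs would discard 240 − 225 = 15 women who had answered.

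**The case against.** The strongest reply is that this is a slip of the pen. The sentence states a between-group aim, the two Wilcoxon tests are easily confused, and the general rule shows that the authors had two-sample methods in mind. If returns differ between arms, software will refuse the test, so the mistake would probably be noticed before publication. Much of this stands. A naming slip is the likeliest explanation, although the article cannot prove it. The text still names the wrong test, so this is a misstatement and not a detail left to an analysis plan.

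A reader might infer that the maternal-satisfaction result will be invalid, or that its p-value could have no valid meaning. The documents do not support that. It assumes literal application, and even then random pairing roughly keeps the type I error. The 73% figure arises only if both arms are sorted before pairing, which nothing in the article suggests. Unequal returns are likely but are nowhere stated.

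**Conclusion.** The point holds in a limited form: a paired test is named for a comparison of two independent, unmatched groups, and nothing in the article corrects or justifies it. That conclusion needs no assumption beyond the stated design.

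If the test were applied as written, the result would depend on an arbitrary pairing, returned questionnaires would be lost whenever the arms returned different numbers, and power would fall slightly (54% against 58% in the example). These sizes rest on assumed ratings and return numbers and should be read as illustration.

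The reach is confined to the maternal questionnaire, including the secondary endpoint of satisfaction with fetal monitoring. The caesarean section comparison and the sample size do not use this test, so it would be wrong to infer a threat to the trial's main conclusion. Severity: a clear but minor correction.

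**What to change.** In the Analysis section, and in any analysis plan that repeats the sentence, replace *Wilcoxon signed rank test* with *Wilcoxon rank-sum (Mann-Whitney) test*. That alone cures the error.

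Because randomisation is stratified by parity, the trial team could instead use the stratified rank-sum (van Elteren) test or a proportional-odds model with parity as a covariate. These are optional refinements and not part of the correction.

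The cost is one line of text. Data collection, participants and sample size are unaffected, and the change can be made at any time before the questionnaire data are analysed.

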### Independent data monitoring and safety committee (DSMC)

The DMSC (to be convened) will include as a minimum an experienced researcher, a statistician and other personnel with extensive research experience. The Committee will conduct the interim analysis when 50 % of the sample has been recruited and their outcomes are known. A recommendation to stop or modify the trial will be made to the Steering Committee if: (i) it is beyond reasonable doubt that the probability of finding a difference in caesarean section rates between groups is <0.001; or (ii) serious adverse events are worse in one group than another.

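### Interim stopping rule (i) is worded as a futility condition, which does not fit the reduction of alpha to 0.049 for an interim test of a difference

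*Protocol article*

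**What the plan says.** Three statements in the protocol article bear on the interim look.

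- **Timing** (Independent data monitoring and safety committee): "The Committee will conduct the interim analysis when 50 % of the sample has been recruited and their outcomes are known".
- **Rule (i)** (same section): a recommendation to stop or modify goes to the Steering Committee if "it is beyond reasonable doubt that the probability of finding a difference in caesarean section rates between groups is <0.001". Rule (ii) concerns serious adverse events and carries no number.
- **Alpha** (Sample size calculations): the trial is sized with "alpha 0.049 (to allow for one interim analysis" and 90% power, and "a sample size rounded up to 300 in each group is required".

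The Analysis section says that "Proportions will be compared by Chi-squared analysis, risk ratios and their 95 % confidence intervals", and it also names logistic regression for the caesarean section comparison. No section states an interim p-value threshold, and none says whether testing is one- or two-sided.

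**The concern.** A p-value is the probability, if there is no true difference, of data at least as extreme as those seen. It is not the probability of finding a difference. As worded, rule (i) is met when finding a difference has become nearly impossible, so it describes stopping for futility.

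That does not fit the sample size section. A futility look spends no alpha, because it offers no extra chance to reject the null hypothesis. Lowering the final alpha makes sense only if the interim look can declare a difference.

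Rule (i) is the only numerical stopping criterion in the document, and the committee has yet to be convened, so its members will have to take the criterion from this text. If they follow it literally, they have no efficacy boundary. If they use the probable intended rule, they must first reverse the plain meaning of the sentence.

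**Working it through.** **Inputs.** Caesarean section rates "from 38 % of women who exhibit a non-reassuring CTG during labour to 25" per cent; 300 per group; power 90%; alpha 0.049 (all from Sample size calculations). Allocation is 1:1 (Randomisation and group allocation). One look at 50% of the sample, so 150 per group and information fraction t = 0.5. Two-sided testing is assumed, since the document does not state it.

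**1. The plan's own figures.**
- Alpha: 0.05 − 0.001 = 0.049, exactly the stated value. The 0.001 of rule (i) is the part removed.
- Sample size at two-sided alpha 0.049 and 90% power, with c = 1.9685 and mean rate 0.315: n = [1.9685·√(2·0.315·0.685) + 1.2816·√(0.38·0.62 + 0.25·0.75)]² / 0.13² = 268 per group, or 283 with continuity correction. Both are compatible with rounding up to 300.
- Power at 300 per group: 93.0%, or 91.7% with continuity correction.

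**2. Probable intended reading: stop if interim p < 0.001, final test at 0.049.**
- Boundary: |z| > 3.29. At 150 per group this is an observed difference of 3.29·√(2·0.315·0.685/150) = 0.176, or 17.6 percentage points.
- Chance of crossing under 38% v 25%: Φ[(0.13 − 0.1765)/√((0.2356 + 0.1875)/150)] = Φ(−0.88) ≈ 0.19.
- Overall two-sided type I error, from the bivariate normal with correlation √0.5: 0.0492. The simple sum 0.001 + 0.049 gives the upper bound 0.050.

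**3. Literal reading: stop if the probability of finding a difference at the final test is < 0.001.** Write m = z√t + θ(1 − t), where z is the interim statistic and θ is the assumed drift at full information. Given the interim data, the final statistic is normal with mean m and variance 1 − t = 0.5.
- *A difference in either direction.* The probability of ending outside ±1.9685 is smallest at m = 0, where it is 2·[1 − Φ(1.9685/√0.5)] = 2·[1 − Φ(2.784)] = 0.0054. It cannot fall below 0.54% whatever effect is assumed, so 0.001 is never reached.
- *A difference in favour of lactate, current trend* (θ = z/√t). The probability is 1 − Φ[(1.9685 − 1.4142z)/0.7071]. At z = 0 it is 0.27%. It equals 0.001 when 1.4142z = 1.9685 − 3.0902·0.7071 = −0.217, so z ≈ −0.15, close to a null result.
- *A difference in favour of lactate, design effect* (θ = 0.13/√(0.4231/300) = 3.46). The probability is 37% at z = 0, 1.0% at z = −2 and 0.04% at z = −3. It reaches 0.001 at about z = −2.75, a strongly adverse result.

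| Reading of rule (i) | Fires when |
|---|---|
| Literal, either direction | never |
| Literal, benefit, current trend | z below about −0.15 |
| Literal, benefit, design effect | z below about −2.75 |
| Interim p < 0.001 | \|z\| above 3.29 |

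No literal reading fires on strong interim evidence of benefit. The p-value reading does.

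**The case against.** The strongest reply is that the document lets a reader recover the meaning. It gives the threshold (0.001), the comparison (caesarean section rates between groups), the timing (half the sample) and a final alpha of 0.049, and only an interim p < 0.001 fits all four. The committee must include a statistician, it only makes a recommendation, and a charter or analysis plan may give the exact boundary. This stands as an account of intent, and it makes literal misapplication less likely. It does not repair the sentence: the document states a rule and states it wrongly, which is different from leaving a detail to a later document.

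A reader might infer several stronger things that the document does not support.

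- *That the literal rule can never be met.* This holds only if a significant result in either direction counts. The word used in rule (i) allows that, but the Aim and Hypothesis are framed as a reduction, and on that reading the rule can fire.
- *That type I error is uncontrolled, or that the alpha or sample size is wrong.* On the literal two-sided reading the trial runs to 600 and is tested at 0.049, which is valid and slightly conservative. On the intended reading the overall error is 0.0492. The unneeded adjustment costs at most 0.001 of alpha.
- *That a committee using p < 0.001 would be inventing a rule.* Every element is present except the statement that the quantity is a p-value.
- *That the protocol specifies a two-sided Haybittle-Peto boundary.* The figures match one, but neither term appears.

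**Conclusion.** The concern holds as a wording error in a decision rule. Rule (i) as written is a futility condition and gives no efficacy boundary, while the alpha of 0.049 presupposes one, so the two sections must be reconciled. The practical loss from following the text literally on the two-sided reading is the chance of an early stop for a large effect, about 19% under 38% v 25%. On the benefit-only readings, the rule would instead prompt a stop on null or adverse data. Type I error is not inflated on the literal two-sided or the intended reading, and alpha and sample size need no change.

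These figures assume two-sided tests, normal approximations, 150 per group at the interim and 300 at the end. That p < 0.001 was intended is an inference from 0.05 − 0.001 = 0.049; the document does not say it.

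**What to change.** Restate rule (i) so that it agrees with the sample size section. For example: a recommendation to stop or modify will be considered if, at the interim analysis on 50% of the sample, the p-value for the between-group difference in caesarean section is below 0.001; the final test of the primary endpoint will use alpha 0.049.

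The sponsor should confirm two points that the document leaves open:

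- whether both tests are two-sided, as assumed here;
- whether the interim p-value comes from the chi-squared test or the logistic regression, since the Analysis section names both.

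If a futility rule was meant, the protocol should say so, define the probability and the effect it is calculated under, and remove or separately justify the 0.049.

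The cost is one sentence in the protocol, carried into the committee's charter. Alpha, sample size and the timing of the look are unchanged.

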### Personnel

We are an experienced team with a strong track record in fetal welfare assessment, including the only NHMRC-funded Australian multicentre randomised trial of fetal oximetry, with its related Cochrane systematic review [49–52, 59]. Our team includes authors of the Cochrane systematic review of intrapartum lactate, co-authors of the RWH Clinical Practice Guideline for fetal blood sampling, the Medical and Midwifery Directors of Birth Suite, obstetric care team leaders, an Epidemiologist, and Neonatologists with experience in large, international randomised trials.

The Steering Committee will be chaired by [name] and will comprise the experienced team of named investigators, with relevant experience in midwifery, obstetrics, neonatology, and RCTs. The Data Management Team will comprise the Chief Investigators and Associate Investigators and the Clinical Research Midwives. Clinical Research Midwives will conduct the trial on a day-to-day basis, during office hours. A statistician will be contracted to assist in setting up and maintaining the database, providing data to the data monitoring and safety committee and the interim and final analyses. We will contract a Health Economist to conduct the economic analysis of the trial.

## Discussion

This randomised trial will be a world-first. Fetal scalp blood sampling for lactate measurement following identification of a non-reassuring CTG in labour has the potential to reduce caesarean section rates, without compromising fetal or neonatal well-being. Such a result would mean that the addition of FBSLM can substantially reduce the health and financial burden from birth by caesarean section. This outcome has significant worldwide implications for women’s health during and following childbirth. Avoiding a caesarean section in an index pregnancy will influence the health of the mother in future pregnancies and will influence health service provision.

Notwithstanding the cost of this trial, there are substantial economic savings to be realised should the hypothesis of reducing caesarean section rates be supported by the trial result [60]. Australian public maternity hospitals receive about $5,000 from the government for each caesarean section, i.e. twice the amount allocated for a vaginal birth [61]. Even if the results of this trial support the hypothesis and were then translated into practice only partially by Australian maternity centres, the cost of the trial would be covered many times over within a relatively short time period of several years. Worldwide, the cost savings would be of great magnitude.

## Abbreviations

CEA: Cost-effectiveness analysis
CTG: Cardiotocography
FBS: Fetal blood sample
FBSLM: Fetal blood sample for lactate measurement
RCT: Randomised controlled trial
RWH: Royal Women’s Hospital, Melbourne, Victoria, Australia
